**Preliminary Studies**

South Africa is an important country to have a SSB tax evaluation due to rising national level SSB consumption trends, rising chronic disease, and being the first African country to implement an SSB tax. Using data from Euromonitor International^67^, we found that SSB sales are rising rapidly across the Africa and Middle East region (Figure 1), and one of the highest per capita consumption rates of SSBs is found in South Africa^12^. While SSB consumption in other high- and middle-income countries is staying constant (Mexico) or decreasing (USA and Chile) in recent years, our data show that SSB consumption in South Africa is rapidly rising and is approaching the levels of other high SSB consumption countries that have implemented SSB taxes. Therefore, there is an urgent need to understand SSB consumption trends and how they may change in response to the new South African SSB tax.

**Figure 1.** Trends in total SSB sales in the USA, Mexico, Chile, South Africa, and the Africa & Middle East Region from 2003-2017. SSBs include categories of regular cola carbonates, non-cola carbonates, liquid concentrates, powder concentrates, juice drinks of <99% juice, sport and energy drinks, and ready-to-drink coffee and tea. All data were derived from the Passport Global Market of Euromonitor International^67^. SSB, sugar-sweetened beverages.

We have conducted descriptive analyses of the baseline demographic and dietary intake data for our study population. Table 1 below displays the baseline SSB intake according to the beverage frequency questionnaire. These data suggest that per capita SSB intake in Langa is much higher than the average per capita SSB intake in South Africa estimated from Euromonitor data in Figure 1.

**Table 1. Mean unadjusted daily volume (ml) of beverage consumption from beverage frequency questionnaire for participants in Langa 18-39y Survey (n=2383), collected at baseline (prior to tax implementation). Data are presented as consumption per capita and per consumer.**

|  | **mL per capita** |  | **% Consumer** | **mL per consumer** |  |
| --- | --- | --- | --- | --- | --- |
| **SSBs** | Mean | SD |  | Mean | SD |
| Water (flavored) | 27 | 114 | 27 | 104 | 207 |
| Concentrates/Cordials | 280 | 460 | 78 | 371 | 496 |
| Sodas (regular) | 403 | 689 | 91 | 449 | 713 |
| Sports and Energy Drinks | 105 | 215 | 62 | 187 | 256 |
| Coffee/tea (sweetened) | 162 | 281 | 65 | 261 | 319 |
| Other* | 40 | 144 | 40 | 120 | 190 |
| Total SSB | 1054 | 1071 | 98 | 1075 | 1071 |
| **Non SSBs** | Mean | SD |  | Mean | SD |
| Water (tap and bottled) | 1289 | 1484 | 99 | 1260 | 1339 |
| Diet sodas | 7 | 45 | 8 | 103 | 139 |
| 100% fruit juices | 58 | 211 | 53 | 115 | 285 |
| Coffee and tea (unsweetened) | 17 | 208 | 5 | 393 | 922 |
| Milk (unsweetened) | 143 | 244 | 71 | 213 | 271 |
| Total Non SSB | 1515 | 1598 | 99 | 1537 | 1599 |
| **Alcohol** | 160 | 1186 | 36 | 446 | 1950 |
| **Total beverages** | 2729 | 2487 | 100 | 2729 | 2487 |

*Beverages include powdered drinks, sweetened milk, and sweetened iced tea.

**Methods**

*Overview*

The overall purpose of this project is to (1) estimate the changes in taxed and untaxed beverage consumption that follow a novel SSB tax implementation; (2) examine SSB knowledge, SSB risk perception, and tax awareness are potential modifiers of the relationship between SSB taxes and SSB consumption; and (3) quantitatively examine the media response to the South African SSB tax. There is a strong empirical basis for conducting this study due to the evidence that SSB taxes have significant effects on SSB consumption^6,7,19,45^, that low knowledge about the health harms of SSBs is associated with increased SSB intake among adults^9^, and that public acceptance of policies are shaped by media framings^53,56,68,69^ and awareness^50^ of the policies. This study is premised upon the conceptual model presented in Figure 4, which shows how the effect of SSB taxes on SSB consumption may be modified by consumers’ knowledge about SSBs and understanding of their relationship with health outcomes as well as awareness of the SSB tax. Additionally, the discussion surrounding new SSB tax implementation generates a media response, the effect of which is partially mediated through changes in consumer knowledge and attitudes as well as other possible mechanisms whereby public discussion of taxes may affect SSB consumption. Thus, both baseline consumer knowledge as well as media influences on consumer knowledge affect SSB consumption. We proceed to outline the approach for each of our aims below.

**
[figure not shown]
**

**Figure 4.** Conceptual Model of the relationship between SSB tax policy, its effect on the media, and the downstream effects on consumer knowledge and tax awareness. These variables are theorized to modify the effect of the relationship between time since taxation and SSB consumption.

*Key databases*

**Langa 18-39y Survey:** Dietary data will be analyzed from the Langa 18-39y Survey of young township adults (n=2383 households), collected by the University of the Western Cape in Cape Town, South Africa. The study population is comprised of adults aged 18-39y living in the Langa township of South Africa. Consent was obtained from 2,383 households to participate in the study from the 2,621 that were requested in the door-to-door recruitment process in the township (90.9% acceptance rate). The Langa township was selected due its proximity to the University of the Western Cape, the stability of the community that could be followed over time, and because it contains a large number of individuals who are heavy consumers of SSBs. Participants resided in a low-income area and received a financial incentive of R30 (USD$2.19) for Shoprite, the supermarket in Langa, after participating.

Data collection began in February 2018, two months before the SSB tax implementation, in order to collect baseline dietary intake data before the SSB tax was implemented. Data are collected at six months and twelve months following the SSB tax implementation to measure changes in the diet of the population. The study instruments, outlined below in Measures and Data Collection, include the 24-hour dietary recall assessment, a beverage frequency questionnaire, and questions related to participant knowledge about SSBs and their associations with increased risk of NCDs.

Participants were recruited using a door-to-door sampling method of all identifiable households in Langa until the target sample size of 2,500 households was achieved. The Langa township has 17,402 households and 52,401 inhabitants (50.4% female), of which 99.1% are of Black African race. The only eligibility criteria applied during data collection was age: participants aged 18-39y were invited to participate in the survey as the investigators were specifically interested in the SSB consumption of young adults. For the baseline data collection, 90.9% of requested participants consented to participate in the study.

**Table 2. Sociodemographic information for Langa 18-39y Survey (n=2,383)
compared to South African National Sociodemographic Statistics 2017**^70^

| **Variable** | **Langa sample**  **(n=2,383)** | **South Africa 2017 (n=56,521,900)** |
| --- | --- | --- |
| **Sex** |  |  |
| Male (%) | 35% | 49% |
| Female (%) | 65% | 51% |
| **Age**  Mean (SD)  Median | 27.9 (6.0)  27.0 | --  26.3 |
| **Race (% Black African)** | 99.1% | 80.8% |
| **Male overweight/obese* (%)** | 25% | 31% |
| **Female overweight/obese* (%)** | 69% | 68% |
| *Overweight/obese defined as BMI ≥ 25. | | |

*Measures and Data Collection*

Data on dietary intake, knowledge and beliefs about SSBs were collected at each time point. For the **diet assessment**, 24-hour diet recalls were conducted by interviewers with nutrition training. Participants reported what foods and drinks were eaten, how foods and beverages were prepared and whether anything was added, and the quantity consumed. Participants were prompted to recall all foods and beverages consumed at six defined time periods throughout the day including: Breakfast consumed between waking up until 9:00, Mid-Morning consumed between 9:00-12:00, Lunch consumed between 12:00-2:00pm, Afternoon consumed between 2:00pm-5:00pm, Supper Time consumed between 5:00pm-sunset, and all other consumption after supper, before bed, and throughout the night. All consumption that occurred during these specified periods was recorded, and no distinction was made between eating occasions (e.g. snacks versus meals). Participants also reported a binary indicator of yes/no for whether this was a usual day of eating for them and if not, what was the reason that intake was unusual. For the **beverage frequency questionnaire** (for simplicity will be referred to as FFQ), participants were asked about two components of their beverage intake: the most common serving size consumed and frequency of intake. For frequency, they were asked “During the past month how often did you (personally) consume any of the following beverages” for each beverage category presented in Table 3, after which they were asked the most common volume (mL). From this survey, baseline beverage intakes from beverage categories are presented in Table 1 above.

After completion of the dietary intake assessment, participants completed a **knowledge and attitudes questionnaire**. This survey asked whether the participant could classify the beverage categories listed in Table 3 as either SSBs or non-SSBs as a demonstration of their knowledge of beverages containing added sugar (hereafter referred to as “knowledge”). Participant knowledge about SSBs was measured using a 1-3 scale for each beverage category listed in Table 3. Participants were asked whether each beverage category was (1) not sugary, (2) somewhat sugary, (3) sugary, or (4) do not know to determine the ability to identify SSBs among beverage categories. Next, after participants were given a definition of SSBs, they were asked to what degree SSB consumption increases the risk of a number of chronic diseases and risk factors including diabetes, high blood pressure, obesity, dental problems, and cancer (hereafter referred to as “risk perceptions”). The degree to which SSBs increased the risk of these conditions could be answered as (1) Not at all, (2) A little, (3) Somewhat, (4) A lot, or (5) Not sure. To assess perception of the tax, participants were asked (1) whether they were aware of the SSB tax (yes/no) and (2) whether they supported the taxation of unhealthy foods and beverages, answerable with strongly oppose, oppose, agree, or strongly agree. Finally, participants were asked whether they intended to reduce their consumption of any of the categories in Table 3 or their SSB consumption overall (“intentions”). Only one diet assessment and one knowledge questionnaire were completed for a single individual within a given household. If there was more than one person in the household, then the older individual (usually mother or grandmother) completed the household level questions. There were no households within which multiple individuals completed these assessments. At both 6 and 12 month data collection periods, participants were asked whether they had been previously surveyed, and if so, at which time period.

In addition to these individual-level data outlined above, another questionnaire was completed using household-level data. Socioeconomic status was assessed according to the SAARF Living Standards Measure (LSM), developed by the South African Advertising Research Foundation (SAARF). The LSM has 10 levels for the South African population, and the score development has been described elsewhere^71^. Our collaborator states that the majority of our population is LSM 5 or lower, which correspond with the bottom 45% of the country^72^, but we still need to verify the distribution of the LSM in our data. The measures necessary for the LSM were collected at baseline, 6 months, and 12 months.

Data: Beverage classification system

To group beverages, we will use a system previously developed to classify beverages in the US^73^ and Mexico^74^, adapted to the South African context. This allows us to compare beverage categories across countries while also ensuring that the beverage groups reflect South African’s typical beverage consumption patterns and that nutritionally similar beverages are grouped together. We will classify beverages into ten broad categories: 1) Water (bottled or tap) and flavored water (either sweetened or unsweetened); 2) cordials and concentrates 3) nectars; 4) energy and sport drinks; 5) regular sugar sodas or soft drinks; 6) diet sodas; 7) 100% fruit juice drinks; 8) coffee and tea; 9) milk and dairy products; and 10) powdered drinks. Table 3 contains descriptions of each beverage analysis category. Each of these categories will be further designated as either taxed or untaxed according to whether they contain added sugars above (taxed) or below (untaxed) the 4g/100ml threshold. Because the amount of tax increases with each gram of sugar, we may also consider further dividing taxed beverages into two categories: taxed (>= 4g/100mL and <8 g/100 mL) and high-taxed (>=8 g/100 ml).

**Table 3. Beverage groups used for classification**

| **Beverage Group Name** | **Beverage group description and examples** |
| --- | --- |
| ***Taxable*** | Beverages that are not exempted, and therefore potentially taxable |
| Flavored water | Still or sparkling water with added flavoring or sweeteners |
| Cordials/concentrates | (e.g. Oros, Fusion, Wild Island) |
| Nectars | Nectars or canned juices that contain fruit (e.g. Tropica, Cabana, Halls, Elvin, Dalys, Take5) |
| Sports and Energy drinks | Energy (e.g Score, Red Bull, Monster) and Sports (e.g. Energade, Powerade, Lucozade) |
| Regular soda or soft drinks | (e.g. Coca Cola, Sprite, Fanta, Stoney Ginger Beer, Cream Soda, Dry Lemon, Jive, Twizza, Refresh) |
| Sweetened milk and dairy products | Sweetened & flavoured: (e.g. Nesquik, Steristumpi, Yogisip) |
| Coffee / tea | Sweetened or unsweetened: (bottled or served; including cappuccino etc) Store bought or home prepared coffee and tea without added sugar |
| ***Untaxable*** |  |
| 100% fruit juice | (e.g. Liquifruit, Ceres, Appletizer) |
| Water (tap, bottled) | Still or sparkling water, without added flavoring or sugars |
| Diet soda / artificially sweetened (noncaloric) | (e.g. Coca Cola Light, Tab, Sprite Zero) |
| Unsweetened milk and dairy products | Unflavored and unsweetened: (e.g. full cream / low fat / fat free / amasi) |
| Powdered drinks | (e.g Game) |

*Linking Food Composition Tables to Beverage Categories*

Accurate food composition tables (FCTs) are necessary to calculate nutrient intakes and total calories from 24-h recalls and FFQs. As a result, inappropriate FCTs for a study population can lead to substantial error in estimations of nutrient intake^75,76^. Because policies such as taxes tend to incentive reformulation, the use of an up-to-date RCT that reflects a rapidly changing food supply is especially important for evaluating policy effects on dietary intake. One key innovation of our study is that along with UWC, we will develop up-to-date FCTs for South African beverages before and after the tax, which will be then linked with the dietary assessment instruments. This will ensure that we are able to understand which beverages are taxed/untaxed at each point in time, and therefore to estimate mean volume and calories from taxed and untaxed beverages in our population before and after the tax. The FFQ contains categories exactly as written in Table 3. Therefore, we will be able to use our updated FCT in analyses using both the 24-h recall and the FFQ. We will also be able to analyze taxable versus untaxable beverages using the FFQ, given that questions make distinctions between taxable beverages and beverages that are specifically exempted.

First, **nutrition facts panel data** was collected by UWC in February and March 2018 (the two months prior to tax implementation). Fieldworkers from UWC took photos of packaged foods in grocery stores (e.g. Shoprite, Checkers, Pick N Pay, Spar, Woolworths), which contained information including barcode, name, size, nutrition, ingredients, and preparation instructions for various beverage brands included within the beverage types listed in Table 3 below. Next, research assistants at UNC linked UWC’s NFP data to FCT beverage codes, e.g. records for various brands and flavors of regular/caloric soda would all be linked to one FCT code for regular/caloric soda. Then, programmers at UNC created an **average nutrient profile** for each **food composition table beverage code**, weighted by the household purchase data from Kantar World Panel (with beverage records with higher purchases contributing more to the nutrient profile), to better reflect the beverages purchased (and consumed) during their time period of collection. Our created food composition table (the UWC-UNC FCT) beverage codes will therefore have values for total sugar concentration, allowing us to assign to them taxation status according to South African law. **Taxation status** will be determined by a two-step process. First, we ask the question of whether the product category is taxable, as 100% fruit juice and milks are exempted^77^. Among those beverages that are taxable, those with a total sugar concentration greater than 4g/100ml are classified as taxed and those with 4g/100ml or less are untaxed. Once the food composition table beverage codes are complete and assigned taxation status, they can be **linked to the beverages reported from the two dietary assessment instruments using beverage codes**. This combination of the updated UWC-UNC FCT with diet assessments will allow us to estimate volume and energy intakes from taxed and untaxed beverage categories and subcategories in our study population.

In addition to this baseline food composition table, we will also develop a renewed FCT using nutrition facts panel data collected 12 months after the tax (March 2019) to account for potential reformulation that has occurred since the tax was implemented. Using the same baseline FCT at both time points will show behavioral change only, since we effectively assume no reformulation by keeping the same FCT. However, using the 12-month updated FCT allows us to understand how our analysis may be affected by reformulation. The approach is outlined in greater detail in the Aim 1 Analysis Plan below.

*Study Power*

This study is powered to detect a mean difference of 6% in SSB intake in our population by 12 months compared to baseline, with 80% power at an alpha level of 0.1. Baseline data from the beverage frequency questionnaire suggests that SSB consumption is 872 ml/day (SD 603); our study would require 1,913 subjects to detect a 6% reduction in SSB intake.

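### Table 3 puts powdered drinks under Untaxable, against the protocol's own exemption rule, so they may never reach the 4 g/100 ml test

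*Protocol*

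**What the plan says.** The protocol assigns tax status in three places.

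- **Table 3** has a Taxable and an Untaxable block. The Taxable block is defined as "Beverages that are not exempted, and therefore potentially taxable". Powdered drinks ("Powdered drinks | (e.g Game")) stand in the Untaxable block, with 100% fruit juice, plain water, diet soda and unsweetened milk. Sweetened milk stands in the Taxable block: "Sweetened milk and dairy products | Sweetened & flavoured: (e.g. Nesquik, Steristumpi, Yogisip").
- **Linking Food Composition Tables to Beverage Categories** gives a two-step rule. Step 1: "First, we ask the question of whether the product category is taxable, as 100% fruit juice and milks are exempted". Step 2, for the drinks that remain taxable: "those with a total sugar concentration greater than 4g/100ml are classified as taxed and those with 4g/100ml or less are untaxed".
- **Data: Beverage classification system** lists ten broad categories, with powdered drinks as the tenth, and says: "Each of these categories will be further designated as either taxed or untaxed according to whether they contain added sugars" above or below the threshold.

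The FCT section also states that the beverage frequency questionnaire (FFQ) uses the categories of Table 3, and that a taxable-versus-untaxable analysis is possible because its "questions make distinctions between taxable beverages and beverages that are specifically exempted". Comparison of diet assessment methods then names taxable and untaxable beverage calories among the key variables to be estimated from both the 24-hour recall and the FFQ. The Aim 1 Outcomes section makes taxed and untaxed volume and calories the primary outcomes.

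**The concern.** Tax status defines the Aim 1 outcomes, so each category needs one status. Powdered drinks have two. Under Table 3 they are exempt and their sugar content is never examined. Under the two-step rule they are not among the named exemptions and go to the sugar test.

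The choice affects how substitution is read. Someone who replaces a taxed soda with a sugared powdered drink has moved between sugary drinks. One rule records that as a move out of the taxable group and the other does not. The main hypothesis is a 6% fall in taxed SSB intake at 12 months, so this kind of switch has to be classified in one fixed way.

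A lesser point of the same kind concerns dairy. Step 1 exempts milks without qualification, while Table 3 treats sweetened milk as taxable.

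**Working it through.** No stated sample size, power or alpha depends on this point, so there is no figure of the plan to reproduce. The check sets the texts side by side and then uses Table 1 for scale.

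**Status of powdered drinks by source**

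| Source | Status |
| --- | --- |
| Table 3 | Untaxable |
| FCT section, step 1 | not named as exempt, so taxable |
| FCT section, step 2 | taxed if above 4 g/100 ml |
| Beverage classification system | split by the sugar threshold like the other categories |

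The other Untaxable rows can be explained from the text. Juice and unsweetened milk are covered by the named exemptions. Plain water and noncaloric diet soda are low in sugar by their own descriptions. Powdered drinks fit neither explanation.

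**Effect of a switch.** Let x mL/day move from taxed soda to powdered drinks.

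- Table 3 governs: taxable intake falls by x and untaxable intake rises by x.
- The two-step rule governs: both drinks are taxable at step 1. Taxed intake falls by 0 if the made-up powdered drink exceeds 4 g/100 ml, and by x if it does not. The protocol does not state its sugar content.

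**Scale, from the baseline FFQ (Table 1)**

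- Powdered drinks are pooled in the Other row, whose footnote reads: "Beverages include powdered drinks, sweetened milk, and sweetened iced tea".
- Other = 40 mL/day per capita; total SSB = 1054 mL/day.
- Share of the pooled group: 40/1054 = 3.8%.
- The powdered share of the 40 mL/day is not given, so it lies between 0 and 40 mL/day.
- For illustration, with assumed switches:
  - x = 10: 10/1054 = 0.9% of SSB volume
  - x = 20: 20/1054 = 1.9%
  - x = 40: 40/1054 = 3.8%

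For comparison, the hypothesised 6% fall is 0.06 × 1054 = 63 mL/day on this base, or 0.06 × 872 = 52 mL/day on the mean used in Study Power.

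**Sweetened milk.** Step 1 read literally exempts it; Table 3 does not. If step 1 means plain milk only, the two agree.

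**The case against.** Several points count against the concern.

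- *The exemption clause may not be exhaustive.* It is a short explanatory clause that cites the levy document and does not claim to be complete. Water and diet soda are also in the Untaxable block without being named there. This stands in part: absence from the clause does not prove the row wrong. It does not explain the row either, because powdered drinks, unlike those two, are not low in sugar by description.
- *The beverage classification sentence is loose.* Read literally, it would also send exempt juice and milk to the threshold. It therefore supports the point without settling it.
- *Table 1 sorts by SSB status, not by tax status.* This is correct. A drink can be an SSB and untaxed, so Table 1 is used here only for scale.
- *Substitution would be visible.* Untaxed intake, subcategories and total beverages are also analysed, so a rise in powdered drinks could be seen. This limits the harm but leaves the taxed outcome ambiguous.

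A reader might also infer three stronger things that the protocol does not support.

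- *That Table 3 has two categories the wrong way round.* The word milks can mean plain milk, which agrees with Table 3's split of dairy into sweetened and unsweetened.
- *That the same drink is taxed in one instrument and untaxed in the other.* The FCT section links one FCT-assigned taxation status to both instruments. A disagreement could arise only where the FFQ taxable/untaxable split follows Table 3 and the recall does not.
- *That up to 63% of the target effect is at risk (40/63).* That ratio sets the baseline volume of three pooled drink types against a change. The base is also total SSB from the FFQ, not taxed intake from the recall, which is the main outcome.

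**Conclusion.** The contradiction over powdered drinks is real. Table 3 exempts them, the two-step rule does not, the classification section sends them to the threshold, and no reason is given. It matters wherever Table 3 decides status, most clearly in the taxable/untaxable analysis. For taxed volume and calories from the recall, it depends on whether step 1 is taken from Table 3 or from the FCT section.

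The size is small and cannot be determined from the protocol. Powdered drinks are somewhere between 0 and 40 mL/day of a group that is 3.8% of baseline FFQ SSB volume, and each 10 mL/day switched is about 0.9% of that volume. The effect on taxed intake assumes that the made-up drink exceeds 4 g/100 ml.

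A reader might conclude that Table 3 is the text in error. The protocol does not show what status the levy gives powdered drinks. If they are legally exempt, a move from soda to powdered drinks is a genuine fall in taxed intake and the FCT section needs the correction. The sweetened-milk mismatch may be no more than loose wording, but it should be settled at the same time.

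**What to change.** Adopt one category-to-status list and have Table 3, the classification section and the FCT section all refer to it.

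- Check the list against the levy document already cited in the FCT section.
- Send powdered drinks to the 4 g/100 ml test unless that document exempts them. If it does, add them to the exemptions named in step 1.
- State whether exempt milks include sweetened and flavoured milk, and align Table 3 with the answer.
- Use the same list for the FFQ and the 24-hour recall at baseline, 6 months and 12 months.

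The cost is an edit to one or two rows of Table 3, a clarification of step 1 and the matching change to the lookup. No new data are needed, and reported totals would be expected to shift only slightly.
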